# Summary

## Study title

Spanish Registry of Pregnant Women with COVID-19

## Protocol number and version

Number 55/20. Version V8.

## Funding

Neither the hospitals nor the participating investigators will receive any financial compensation for their collaboration. A bank account has been opened at the hospital's Biomedical Research Foundation to receive donations: COV20/00072 - SARS-CoV-2 and the COVID-19 disease Call financed by the Carlos III Institute of Health and co-financed with ERDF funds.

## Abstract

**Rationale:** Knowledge about the impact of the SARS-CoV-2 virus on pregnancy is still scarce and all current recommendations are based on less than 100 cases published in the literature. To identify moderate effects (such as vertical transmission, obstetric morbidity, foetal death, maternal or neonatal death) and to allow accurate risk estimates, larger sample sizes than those currently available are required.

**Methods:** Prospective observational study of pregnant women in whom SARS-CoV-2 infection is suspected at any time during pregnancy with positive test results for SARS-CoV-2, in order to create a registry of baseline characteristics of the pregnant woman, aspects related to the course of pregnancy and delivery, and related to the new-born, with an observation period of up to 14 days after delivery. Subsequently, several phased studies will be conducted to help establish and monitor the set of measures to improve the care of pregnant women.

**Discussion:** The national registry for COVID-19 in pregnancy described here is a tool for sharing and centralizing data related to exposures to SARS-CoV-2 during pregnancy in a structured way. It should speed up the process of prospectively obtaining a large unbiased data set and will collect information at national level.

## Study rationale and background

On 31st December 2019, the Wuhan Municipal Health Commission (Hubei Province, China) reported on a cluster of 27 pneumonia cases of unknown aetiology, with a common exposure to a seafood and live animal wholesale market in Wuhan City, including seven serious cases (1). The first case began on 8th December 2019 with fever, dry cough, dyspnoea, and radiological findings of bilateral pulmonary infiltrates. On 7th January 2020, Chinese authorities identified a new type of virus from the Coronaviridae family as the causative agent of the outbreak, which was subsequently named SARS-CoV-2, and whose genetic sequence was shared by the Chinese authorities on 12th January. The disease caused by this new virus has been called COVID-19 by international consensus (2).

### Clinical course of SARS-CoV2 infection in pregnant women

Pregnant women are known to experience immunological and physiological changes that can make them more susceptible to viral respiratory infections, including COVID-19. Several studies revealed that pregnant women with different viral respiratory diseases had a high risk of developing obstetric complications and adverse perinatal outcomes compared to non-pregnant women, due to changes in immune responses (3,4). We also know that pregnant women may be at risk of serious illness, morbidity, or mortality compared to the general population, as seen in other coronavirus infections.

Coagulation alterations have been described in people admitted to hospital for COVID-19 and, given that pregnancy confers a state of hypercoagulability, it is to be assumed that SARS-CoV2 infection in pregnant women may increase the risk of suffering from thromboembolic events, therefore, depending on the symptoms and other risk factors, they would require heparin prophylaxis (5,6). In Spain, there have been two deaths of patients with COVID-19 who had completed their pregnancies by Caesarean section, although it should be borne in mind that in both cases the Caesarean section was carried out due to severe maternal involvement (7). The causes of these deaths were related to coagulation abnormalities, in the first case due to pulmonary thromboembolism in a context of sepsis and in the second due to abruptio placentae with fulminant coagulopathy (8).

Regarding the period of gestation, no significant differences have been found between the course of the disease depending on the trimester of gestation, although most admissions for COVID-19 have occurred during the second and third trimesters (5,6,9). However, it has been shown that caesarean delivery is an independent risk factor that increases the chances of clinical worsening in pregnant women compared to vaginal delivery (7), both in asymptomatic pregnant women and in those with mild symptoms.

In China, several published studies show that in cases where the pregnant woman had pneumonia or a diagnosis of SARS-CoV-2, the delivery was often completed by caesarean section. The results of the Chinese series on 18 published cases show that 16 have resulted in caesarean section and two in vaginal deliveries. In these series, the patients showed symptoms of the disease (fever and cough) before, during and after delivery (10,11).

In the Chen H study, caesarean section was carried out between days 1 and 7 from the onset of symptoms (mean 3.3 days). One of these cases occurred after the caesarean section and in two cases a non-elective caesarean section was carried out at night (10).

In the study by Zhu H, of the 9 cases, 3 manifested in the postpartum, 2 intrapartum and 4 before delivery. In this series, two vaginal deliveries are published, with one of them being twins in a patient with symptoms (fever and cough) and the other one with symptoms starting in the postpartum period. Delivery occurred between 1 and 6 DAYS after admission (mean 3.5). Of those cases in which the symptoms occurred in the postpartum, between 1 and 3 days elapsed from delivery in this series. One case had a cough and two cases had fever (11).

Although the indications for caesarean sections are not clearly specified in the Chen H study (10), in the Zhu H study 5 were due to foetal *distress*, one case of previous uterine scar and an elective caesarean section due to maternal fever. The author suggests that maternal hypoxemia caused by infection triggers foetal hypoxia and preterm delivery. There are no data on the direct influence of COVID-19 on the intrauterine foetal status (11).

## Vertical transmission

The evidence of vertical transmission (before, during or after delivery by breastfeeding) in women who acquire the infection during the third trimester of pregnancy is scarce and intrauterine transmission of the virus has not yet been totally ruled out (12).

In the Chinese series, 16 out of the 18 pregnant women gave birth by caesarean section and, although the newborns did not show SARS-CoV-2 infection, perinatal infection can have adverse effects on newborns, such as loss of foetal well-being, premature birth, respiratory distress, thrombocytopenia along with impaired liver function and even death (10,11). In Chen H's study, the amniotic fluid (only 6 samples of the 9 caesarean sections), cord and placenta analysis was negative for COVID-19, but in this series there have been no normal deliveries with prolonged dilations or passage of the foetus through the birth canal (10).

Regarding the transmission of the virus through breastfeeding, there are still contradictory data regarding the presence of the virus in breast milk. However, in theory, breastfeeding is not contraindicated in women with COVID19 (13,14).

## Rationale

To date, few studies have described the impact of the SARS-CoV-2 virus on pregnancy, particularly infection occurring during the third trimester of pregnancy. The impact of the virus during the first and second trimesters of pregnancy remains unknown and must be urgently determined. All current recommendations are based on less than 50 cases published in the literature, with speculations on different aspects of management. To identify moderate effects (such as vertical transmission, foetal death, maternal or neonatal death), larger sample sizes than those currently available are required to allow accurate risk estimates. The national registry for COVID-19 in pregnancy described here is a tool for sharing and centralizing data related to exposures to SARS-CoV-2 during pregnancy in a structured way. It should speed up the process of prospectively obtaining a large unbiased data set and will collect information at national level.

## Study hypothesis and objectives

### Hypothesis

The COVID 19 disease affects pregnancy and has an influence on maternal and perinatal morbidity and mortality

### Objectives

This study focuses on the creation of a registry of pregnant women with COVID-19 infection, which will help establish and monitor the set of measures to improve their care.

### Primary objective

Collect and analyse COVID-19 cases in pregnant and postpartum women at associated health centres.

### Secondary objectives

1. Establish incidence of COVID-19 infections diagnosed in pregnant women in the Spanish population.
2. Determine the variables that are associated with more maternal and neonatal morbidity.
3. Determine if there is vertical transmission.
4. Evaluate the risk of SARS-CoV-2 infection during pregnancy.
5. Characterize the clinical course of SARS-CoV-2 infection during pregnancy (for example, severity of maternal symptoms, distribution of gestational age at onset, ICU admission, mechanical ventilation, death).
6. Quantify the risk of adverse pregnancy outcomes (e.g., miscarriage, stillbirth, growth restriction) and neonatal outcomes (e.g., NICU, prematurity, death, birth defects).
7. Identify additional risk factors and risk modifiers (e.g., symptomatic infection, SARS-CoV-2 positive amniotic fluid, co-infections).

8. Develop a responsive data collection tool across a network of healthcare facilities to ensure rapid assessment of risks associated with future emerging pathogens and to help develop guidelines on this disease.
9. Strengthen capacity-building in data exchange against emerging pathogens.

The collected dataset will allow a comprehensive characterization of the risks associated with SARS-CoV-2 infection in pregnancy. In the future, the developed structure will allow a rapid assessment of the risks linked to future emerging pathogens.

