## Data sources and work plan

### Patient referral sources

If the doctor in charge considers it appropriate to inform the patient about the existence and purpose of this registry, he/she may do so. At this time, consent will be requested so that the information derived from the regular monitoring of these patients is incorporated into the data registry, and that said information can be analysed and disclosed for scientific purposes in accord with the confidentiality provisions of the current legislation.

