## EXTRACTION OF DATA FROM THE REGISTRY: SUBSTUDIES

Based on the registry prepared, data extraction will be carried out to carry out four sub-studies that address the secondary objectives.

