## Substudy 4. Epidemiological prevalence study

### Objective/s

Determine the prevalence of SARS\_COV2 infection in Spanish pregnant women

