### Design

Cross-sectional study.

The nQuery Advisor Release 7.0 software was used to calculate the sample size, based on the available data. As we do not have data on the prevalence of COVID-19, we set an expected percentage of 50% (a situation that maximizes the sample size) of asymptomatic women during delivery. We determined the sample size for a COVID-19 delivery prevalence study with an expected prevalence of 50%, a 95% confidence level and 5% accuracy, resulting in a sample size of 1056 pregnant women.

The selection of pregnant women in the sample will follow the distribution of the delivery rate by communities and hospitals in Spain according to the INE data for 2018 (Appendix 3) (15). Subsequently, a simple random selection procedure will be carried out in each site, creating a numerical list of the women to be included in the sample (Appendix 1). Pregnant women will be assigned a consecutive number from one onwards according to their due date. Subsequently, the pregnant women who will be part of the sample will be chosen when the number that identifies them is within the table previously created through the random procedure.

Recruitment: 1st March 2020 to 1st March 2021. Spanish sites collected in the Appendix 1

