### Inclusion criteria:

- Single or multiple gestations of 24 weeks or more without a positive laboratory test for COVID-19 prior to delivery.
- Delivery in a public or private maternity hospital in Spain with a diagnostic test for COVID-19 using PCR Kits within 72 hours prior to delivery or 24 hours after delivery.
- The presence of comorbidity is not an exclusion criterion (asthma, diabetes mellitus, hypertension-preeclampsia, endocrine disorder, dermatological pathology or other obstetric or medical-surgical pathologies).
- Acceptance by the pregnant woman to participate in the study by means of informed consent for group study.

The result of the PCR test on a sample of nasopharyngeal and/or oropharyngeal swab was considered synonymous with exposure/non-exposure, defining a case as any pregnant woman with a positive result, regardless of the symptoms. Those cases with clinical presentation of COVID-19 were classified according to the WHO division for adults into: mild symptoms, mild-moderate pneumonia, severe pneumonia and septic shock (16).

The recommended samples for diagnosis are samples from the upper respiratory tract: nasopharyngeal and/or oropharyngeal swab.

A healthy patient is considered to have a negative PCR in the absence of symptoms. Patients with positive IgM or IgG serology cannot be included. The absence of serology does not prevent classifying the patient as healthy if the PCR is negative.

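### Secondary objective 1 promises the incidence of diagnosed infection in pregnancy, but no substudy as designed can estimate it

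*Protocol*

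**What the plan says.** Protocol, Secondary objectives, item 1: "Establish incidence of COVID-19 infections diagnosed in pregnant women in the Spanish population". The Overall sample size section repeats the aim, naming the unknown percentage of pregnant patients diagnosed as something the study is to find out.

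The Study design section says that sub-analyses of the registry data will address the secondary objectives. The section on extraction of data from the registry speaks of "four sub-studies that address the secondary objectives".

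The nearest substudy is Substudy 4. Its objective is "Determine the prevalence of SARS\_COV2 infection in Spanish pregnant women" and its design is "Cross-sectional study". Its first inclusion criterion is "Single or multiple gestations of 24 weeks or more without a positive laboratory test for COVID-19 prior to delivery", and the PCR must fall between 72 hours before and 24 hours after delivery.

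On entry to the registry, Patient referral sources says: "If the doctor in charge considers it appropriate to inform the patient about the existence and purpose of this registry, he/she may do so". Consent is then requested. The Exclusion criteria remove women whose follow-up is lost before 6 weeks postpartum.

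**The concern.** Incidence of diagnosed infection needs two things: a count of women newly diagnosed in a stated period, and the number of pregnant women at risk (or at least delivering) in that period. The substudy that looks as if it answers objective 1 measures something else. It takes one test at one moment and leaves out women who already had a positive result.

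At stake is the label on the result. A delivery-screening prevalence, or a partial case count over an out-of-period total, could be published as the incidence of diagnosed infection in pregnant women in Spain. This cannot be left to the statistical analysis plan. An analysis plan can choose an estimator, but it cannot reverse an eligibility criterion or create counts that are not collected.

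**Working it through.** The plan gives no incidence figure, so there is none to reproduce. The check is whether any component holds both a numerator and a denominator for objective 1.

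**Where the objectives reappear.** Items 2 to 7 of the secondary objectives each recur in the objective list of Substudy 1, 2 or 3. Items 8 and 9 concern data tools and capacity. Item 1 is the only quantitative objective that no substudy lists. Substudy 4 comes closest, but replaces incidence with prevalence.

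**Each component in turn.**

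| Component | Women included | Why it does not give diagnosed incidence |
|---|---|---|
| Substudies 1 and 2 | PCR-positive only | No women at risk, so no denominator |
| Substudy 3 | Cases plus at most 3 neighbouring PCR-negative deliveries per case | Case share fixed by sampling; with 3 controls per case it is 1/(1+3) = 25% whatever the true frequency |
| Substudy 4 | 24 weeks or more, PCR around delivery, no earlier positive | Point prevalence; earlier diagnoses excluded |
| Whole registry | PCR-positive at any stage of pregnancy, plus controls | Entry depends on the doctor's discretion, consent and 6-week follow-up; no concurrent total of deliveries or pregnancies described |

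Substudy 1 also lists evaluating the risk of infection in pregnancy, but with only positive women it has no denominator for that either.

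**Direction of the Substudy 4 gap.** Take N screened women delivering at 24 weeks or more. Let e have an earlier positive test, and let x of the remaining N − e test positive at delivery.

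- Proportion ever diagnosed: (x + e)/N
- Substudy 4 proportion: x/(N − e)
- Difference: [(x + e)(N − e) − xN] / [N(N − e)] = e(N − x − e) / [N(N − e)]

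The difference is above zero whenever some women were diagnosed earlier and some were never diagnosed. Substudy 4 therefore understates the diagnosed proportion. The size depends on e, which the document does not give and Substudy 4 does not record.

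**The totals available.**

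- 172,000 deliveries at the 100 sites in 2019 (Overall sample size).
- 370,827 births in Spain in 2018 (Appendix 3).
- Recruitment runs from 1 March 2020 to 1 March 2021 (Study design), so both totals come from earlier years.
- 172,000/370,827 = 46.4%. The years differ, so this is only a rough indication that the sites cover under half of national births.

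**The case against.** **The sentence assigning objectives to substudies is not exhaustive.** Items 8 and 9 match no substudy, so it cannot mean that every objective is covered, and the Overall sample size section ties the percentage diagnosed to the registry as a whole. This stands as a reading of that sentence. It does not supply an incidence analysis or a concurrent denominator elsewhere in the protocol.

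**A reader might infer that the registry has no numerator at all.** The document does not support that. Women diagnosed at any stage of pregnancy are its target population and hospitals enrol continuously. Sites with existing cohorts may contribute data if they systematically included screened women whatever the result. Substudy 3 refers to hospitals with universal consecutive screening, and consent may be oral or electronic. The numerator is incomplete, not absent.

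**A reader might infer that 172,000 is the only denominator, or that the plan intends to divide by it.** Neither is right. Appendix 3 gives national births, and the protocol never says that 172,000 will be used this way. Appendix 1, also cited there, was not available for this check.

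**A reader might try to size the gap.** With PCR positive for 2 to 4 weeks and a constant hazard over 38 weeks, cumulative incidence would be 38/4 = 9.5 to 38/2 = 19 times the prevalence at delivery. This does not hold up:

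- The durations are assumptions from outside the document.
- The ratio counts all infections, whereas objective 1 concerns diagnosed ones.
- The protocol dates the first case to 8 December 2019. A woman delivering on 1 March 2020 had at most 12 weeks of possible exposure, which gives 12/4 = 3 to 12/2 = 6. Nobody delivering before about 30 August 2020 could have had 38 weeks.

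Likewise, a 20% to 50% under-count from enrolling 50% to 80% of diagnosed women only restates the assumed enrolment rate.

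**Conclusion.** Wrong as written: the objective and the design assigned to it do not match, and this follows from the protocol's text without any outside assumption. No substudy can estimate the incidence of diagnosed infection in pregnancy, and the registry's own case count is incomplete with no concurrent denominator described.

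The Substudy 4 proportion lies below the proportion ever diagnosed among the same women if any were diagnosed earlier; by how much cannot be computed from the document. For enrolled cases over an earlier year's deliveries, the missing cases pull the ratio down, while the mismatched year could move it either way, so even the net direction is not fixed.

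The point affects one of nine secondary objectives. The primary objective, to collect and analyse cases, does not depend on it.

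**What to change.** Choose one of two changes.

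(a) **Narrow the objective to what Substudy 4 measures:** prevalence of PCR positivity at delivery, at 24 weeks or more, among women with no positive test before the delivery screening window. The inclusion criterion needs rewording at the same time. Read literally, a positive screen in the 72 hours before delivery is itself a positive test before delivery and would exclude the woman; the text should say that it counts as a case.

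(b) **Keep an objective on diagnosed infection and collect the counts for it.** Each site supplies two aggregate numbers for 1 March 2020 to 1 March 2021: deliveries, and PCR-positive pregnant women whether enrolled or not. Report diagnosed infections per 1000 deliveries at participating sites. State that this is a crude ratio, because some women diagnosed in the period deliver outside it or miscarry, and that it describes the participating sites and not all of Spain.

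Under either option, do not report as incidence the Substudy 4 figure, or enrolled cases over the 2019 or 2018 totals.

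The cost is a narrower objective under (a), or two aggregate counts per site with no patient-level data under (b).

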## Study design

Prospective observational registry study of pregnant women with suspected SARS-CoV-2 infection at any time during pregnancy with positive test results for SARS-CoV-2.

A specific database will be developed, which will include the baseline characteristics of the pregnant women, aspects related to the course of pregnancy and childbirth, and the new-born. Vertical transmission will be analysed only by means of a nasopharyngeal swab from the new-born before contact with the mother. This registry sets an observation deadline of up to 14 days after birth for the new-born and 6 weeks postpartum for the mother. The registry will be hosted on a secure https server, this server will be physically located at **OBS Covid Spain** of the company ReserArch which has a contract with the Puerta de Hierro-Majadahonda University Hospital Research Foundation.

Recruitment period will be between 1st March 2020 and 1st March 2021.

After that, different sub-analyses will be carried out with the data extracted in the registry and the secondary objectives will be addressed.

## Definitions

### Definition of case and healthy patient for the study

The result in the PCR test on a sample of nasopharyngeal and/or oropharyngeal swab was considered synonymous with exposure/non-exposure, defining a case as any pregnant woman with a positive result, regardless of the symptoms. Those cases with clinical presentation of COVID-19 were classified according to the WHO division for adults into: mild symptoms, mild-moderate pneumonia, severe pneumonia and septic shock (16).

The recommended samples for diagnosis are samples from the upper respiratory tract: nasopharyngeal and/or oropharyngeal swab.

A healthy patient is considered to have a negative PCR in the absence of symptoms. Patients with positive IgM or IgG serology cannot be included. The absence of serology does not prevent classifying the patient as healthy if the PCR is negative.

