## Study population and selection criteria

For the characterization of the clinical course of SARS-CoV-2 infection during pregnancy, the pre-study sample size calculation has not been carried out, as registry-based studies generally tend to be comprehensive without involving hypotheses.

Patients eligible for follow-up of target population will be any pregnant woman who is suspected or needs to be ruled out as having a SARS-CoV-2 infection at any time during pregnancy with positive test results for SARS-CoV-2 by PCR.

Information regarding each pregnant woman's demographic characteristics, comorbidities and current obstetric history was extracted from the medical history and the patient interview; subsequently, age and race were categorized according to the classification used by the Center for Disease Control and Prevention (CDC) (17).

For the selection of the control group to be collected in the same database, patients with a negative COVID-19 delivery diagnosed by PCR screening at delivery, or less than 3 days before, were considered.

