### Patients

Case eligibility criteria included individuals with laboratory confirmation of COVID-19 infection, irrespective of clinical signs and symptoms or the result of another serological test. Positive RNA PCR test from maternal nasopharyngeal swabs.

The selection of the control group will be collected in the same database, considering patients with negative COVID-19 delivery diagnosed by PCR screening at the time of delivery or less than 3 days before.

The delivery or deliveries that were treated in this site and that occurred within the same day, before and after the case (maximum 3 per case), are included in the control group. If the case were the last delivery of the day, the first ones of the following day could be recruited. If the case were the first of that day, the last one of the previous day could be recruited.

The data collected will be entered at the time they join the registry.

Delivery monitoring: the *outcomes* include perinatal and neonatal events, which were collected at the time of delivery and the days immediately afterward. These perinatal events included gestational age, type of delivery, presence of prepartum or premature rupture of membranes before delivery, as well as any medical complications (thromboembolic events, admission to ICU, maternal death) and obstetric complications (hemorrhagic events and hypertensive disorders), while neonatal events included the 5-minute Apgar score, the pH of the umbilical artery and possible complications such as admission to the NICU and neonatal death in the follow-up period or intrauterine foetal death. The definitions of obstetric pathology follow the international criteria of the ACOG and RCOG (18-21).

Follow-up after delivery: Patient follow-up is carried out by the local investigator over the phone and the medical history is consulted from the time the patient is discharged up to 6 weeks later in order to detect late postpartum complications related to COVID 19. In the case of the new-born, the follow-up is 14 days by the investigating neonatology department by telephone and consultation of the patient's medical history to detect symptoms of COVID 19 symptoms. Complications recorded in the mother during this period (mastitis, endometritis, pulmonary embolism) as well as neonatal death or readmission of the new-born due to COVID were considered *outcomes* of interest and analysed together with those described above.

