#### COVID-19 symptoms

|                                                   |                                 |
|---------------------------------------------------|---------------------------------|
| Mild symptoms (Symptoms reported at birth) | Cough                           |
|                                                   | Fever                           |
|                                                   | Dyspnoea                        |
|                                                   | New olfactory or taste disorder |
|                                                   | Fatigue/malaise                 |
|                                                   | Altered consciousness           |
|                                                   | Headache                        |
|                                                   | Nausea/vomiting                 |
|                                                   | Diarrhoea                       |
| Mild-moderate pneumonia                    |                                 |
| Severe pneumonia                           |                                 |
| Septic shock/maternal mortality            |                                 |

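### The unexposed group has two unreconciled definitions; if the symptom-free one governs, COVID odds ratios may be inflated for complications that themselves cause listed symptoms

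*Protocol*

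**What the plan says.** **Symptom-free rule.** The section Definition of case and healthy patient for the study, which by its heading covers the whole study, says: "A healthy patient is considered to have a negative PCR in the absence of symptoms". The text that follows bars women with positive IgM or IgG and allows a woman without serology to count as healthy if her PCR is negative. The whole paragraph is repeated in Substudy 4, Inclusion criteria.

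**PCR-only rule.** The same Definitions section opens by saying that the PCR result "was considered synonymous with exposure/non-exposure". Study population and selection criteria then describes the control group without any symptom condition: "patients with a negative COVID-19 delivery diagnosed by PCR screening at delivery, or less than 3 days before, were considered". Substudy 3, Patients, does the same: "considering patients with negative COVID-19 delivery diagnosed by PCR screening at the time of delivery or less than 3 days before". It takes the deliveries adjacent to the case, at most three per case.

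**Cases.** Symptoms play no part on this side. The Definitions section is explicit in "defining a case as any pregnant woman with a positive result, regardless of the symptoms", and Substudy 3 admits cases "irrespective of clinical signs and symptoms or the result of another serological test".

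**Use.** Substudy 3, Statistics, makes the odds ratio for the COVID factor, with its 95% CI and significance, the only result of interest from its regression models. Substudy 4, Statistics, also estimates odds ratios.

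**The concern.** A PCR-negative woman with symptoms, and no earlier infection, is a valid control under one rule and not healthy under the other. With 100 sites, both readings could be applied.

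The difference matters because the listed COVID-19 symptoms are not specific to COVID-19. The list in Substudy 3 includes fever, dyspnoea, altered consciousness, headache and "Nausea/vomiting". Severe preeclampsia, HELLP and pulmonary embolism are among the variables compared in Substudies 3 and 4, and they can produce some of these symptoms. That link is clinical judgement; the protocol does not map symptoms to outcomes.

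Under the symptom-free rule, a PCR-negative woman with severe preeclampsia and headache leaves the comparator, while the same woman with a positive PCR stays as a case. This selects on a consequence of the outcome, in one group only. Adjustment for baseline covariates does not remove it. The distortion would run in the direction of the study hypothesis and would fall on the main quantity of Substudy 3.

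**Working it through.** **Step 1: the texts side by side.**

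| Section | Condition on the unexposed woman |
|---|---|
| Definitions, opening sentence | PCR result alone |
| Definitions, healthy patient | Negative PCR, no symptoms, no positive serology |
| Study population and selection criteria | Negative PCR at delivery or under 3 days before |
| Substudy 3, Patients | Same, applied to adjacent deliveries |
| Substudy 4, Inclusion criteria | Repeats both Definitions entries |

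The two control-selection texts do not use the word healthy and do not refer back to the Definitions. Nothing says which rule prevails, which symptoms count, or when they are assessed.

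**Step 2: bias factor if the symptom-free rule is applied.** The plan states no expected odds ratio, complication rate or symptom rate here, so there is no figure to reproduce. Let p be the complication risk, equal in both groups (no true effect). Among PCR-negative women, let s1 be the share with a listed symptom given the complication, and s0 the share without it.

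- Odds among cases: p/(1 − p).
- Odds among retained controls: p(1 − s1) / [(1 − p)(1 − s0)].
- False odds ratio: (1 − s0)/(1 − s1). The risk p cancels.

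**Step 3: check on an explicit table.** Assume 1000 cases, 3000 controls, p = 5%, s0 = 2%, s1 = 50%.

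- Cases: 50 with the complication, 950 without.
- Retained controls: 3000 × 0.05 × 0.50 = 75 with, 3000 × 0.95 × 0.98 = 2793 without.
- Odds ratio: (50 × 2793)/(950 × 75) = 1.96, equal to 0.98/0.50. The result is the same at p = 1% and p = 10%.

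**Step 4: range.** All values of s0 and s1 are assumptions. With s0 = 2%:

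| s1 | False odds ratio |
|---|---|
| 2% | 0.98/0.98 = 1.00 |
| 5% | 0.98/0.95 = 1.03 |
| 10% | 0.98/0.90 = 1.09 |
| 20% | 0.98/0.80 = 1.23 |
| 30% | 0.98/0.70 = 1.40 |
| 50% | 0.98/0.50 = 1.96 |

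Varying s0 from 1% to 10% gives 1.41 to 1.29 at s1 = 30%, and 1.98 to 1.80 at s1 = 50%. If s1 is below s0, the factor falls below 1 (s0 = 5%, s1 = 2% gives 0.97).

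**Step 5: the opposite risk.** Dropping the symptom condition keeps some infected, false-negative women among the controls. Assume a true odds ratio of 2.0 and a 5% risk in uninfected women. The odds in the infected are then 2 × 0.05/0.95 = 0.1053, a risk of 9.52%. If 1% of PCR-negative women are infected, the control risk is 0.99 × 5% + 0.01 × 9.52% = 5.045% (odds 0.0531), and the observed odds ratio is 0.1053/0.0531 = 1.98. At 2% infected it is 1.96.

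**The case against.** The strongest reply is that the operative control rules already use PCR alone. Both control-selection texts omit symptoms, Substudy 3 fills its control group by adjacency of delivery, and the Definitions section itself equates PCR with exposure. On that reading the preeclamptic woman with headache stays a control and no bias arises. This stands as far as it goes: a reader might infer that the comparator must be symptom-free and that the COVID odds ratios are therefore inflated, and the documents do not support that. It does not dispose of the point, because the control texts are silent on symptoms and do not override the study-wide definition. The serology sentence in the same paragraph is worded as an eligibility rule. In Substudy 4 the repeated paragraph is the only local description of a non-case, although the PCR-equals-exposure sentence is repeated there too.

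Second, the protocol never makes its symptom list a filter for controls. That is correct, and the missing list and time point are part of the defect.

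Third, timing limits the mechanism. Substudy 3 describes mastitis, endometritis and pulmonary embolism as complications recorded in follow-up after discharge. Symptoms from such later events could not remove a woman who was classified around delivery. This stands, and it confines the concern to complications evident by then. Premature rupture of membranes has little or no link to the listed symptoms.

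Fourth, the size rests on assumed rates, and low rates give trivial bias. This also stands. For broader outcomes such as preterm delivery or NICU admission, any effect would be diluted by the many events without a listed symptom.

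**Conclusion.** The point holds as a contradiction with a conditional consequence. The unexposed group is defined in two ways that are not reconciled, and cases enter regardless of symptoms under both. If the symptom-free definition governs, odds ratios may be inflated for severe preeclampsia, HELLP, and pulmonary embolism before or at delivery, with little or no effect on premature rupture of membranes or on later endometritis and mastitis.

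The size cannot be derived from the protocol. Under no true effect and an assumed 2% symptom rate without the complication, the false odds ratio runs from 1.03 to 1.96 as the rate with the complication goes from 5% to 50%. It is 1.00 if the two rates are equal, or if the PCR-only rule is the one applied. These figures also assume that every woman with a listed symptom at classification is dropped from the PCR-negative side.

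**What to change.** State one comparator definition in four places: Definition of case and healthy patient for the study, Study population and selection criteria, Substudy 3 Patients, and Substudy 4 Inclusion criteria. It should require a negative PCR in the delivery window given for that substudy, no earlier positive PCR and no positive serology, with no symptom condition.

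The history and serology conditions need to stay. A definition by delivery PCR alone would admit the ex-symptomatic or cured women described under Definitions of symptomatic and asymptomatic patient, who may be PCR-negative by then.

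Record symptoms in PCR-negative women as a variable, with the symptom list and assessment time stated. Use the symptom-free comparator only as a sensitivity analysis.

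The cost is amended wording and one extra analysis. The statistical downside is that a few false-negative women remain among the controls, which biases slightly toward no effect: a true odds ratio of 2.0 becomes 1.98 to 1.96 under the assumptions in the working.
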